
### Recruitment {15}

The recruiting will start with the pre-selections of subjects with occasional gingival bleeding. These subjects are screened for further eligibility for the intervention study. The continuous recruitment will address primarily patients of dental school and university students.

### Assignment of interventions: allocation

#### Sequence generation {16a}

The main aim of the randomized allocation process will be to *equalize* both intervention groups on basis of the initially documented oral health data under the inclusion of caries and gingival/ periodontal status [2, 9, 26, 27, 37, 42, 47, 58, 66]. This requires an analysis of dental screening and re-examination data. On basis of the gingival health data, a randomized allocation list will be established.

#### Concealment mechanism {16b}

In principle, all participants will receive the same preventive measures owing to ethical reasons. Following the allocation of all subjects to one of the intervention groups, each participant will be informed by telephone about the appointment for the phase 2 baseline examination. As the protocol for the two groups—immediate and delayed intervention—cannot be blinded for the study team and participants, no efforts will be made to conceal this information.

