### Trial design {8}

The design of this randomized clinical trial is a “waiting control group design”, which compares the immediate intervention group with the delayed intervention group. The latter one will serve as a control group. The intervention cannot be blinded, but the outcome measure (lung function tests) is blinded, because the technician does not know to which group (immediate or delayed intervention) the subject belongs to. Moreover, the absence of any intervention in subjects with gingivitis would be unethical, but an intervention delayed for 4 weeks seems acceptable.

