The power analysis focuses on the second part of the study, in which two different treatments are realized, whereby in both arms assessments before and after treatment are performed (Fig. 4). As the control treatment may be expected to be associated with a positive change, although smaller than in the target treatment group, the assumed effect is taken to be greater than zero. Thus, relative effects of m1 = 2 and of m2 = 1 are assumed for the target treatment and the control treatment group, respectively, in units that can be adapted to those of the outcome measures. There are no sufficient data on the (longitudinal) variation of measured values due to either methodological or biological sources. The power analysis is performed with an assumed variance of 1.5 for each assessment, in units identical to those of the effects and corresponding to a standard deviation (SD, square root of variance) greater than 1 but less than 1.5, which we consider as a reasonable value. Assuming that the measurement errors are independent in the pre and post-assessments, the variances add up for the pre-post differences, resulting in a total variance of each of the two differences of 3, i.e. an assumed standard deviation of about 1.7 (square root of 3) for each difference. Thus, we have two groups with expected effects of 2 or 1, both with standard deviations of about 1.7. This seems a reasonable basis for analysis, whereby the mean differences observed in the two treatment arms have to be compared in a standard 2-means comparison based on normal distributions. The comparison is performed two-sided in order to be on the safe side, although the hypothesis is that treatment arm 1 is more effective than treatment arm 2. Requiring a power of 90% (beta = 0.1, error of the second kind) at a significance level of 5% (alpha = 0.05, error of the first kind), the assumed parameter values result in sample sizes of *n* = 61 for each of the two treatment groups. When assuming variances of either 1 or 2 instead of 1.5 for each of the assessments, the required group sizes would be *n* = 42 or *n* = 84, respectively. In the latter case, a sample size of *n* = 63 in each group would still be sufficient for alpha = 0.05 at a power of 80% (beta = 0.2), which is often considered as sufficient in clinical trials. Thus, based on reasonable assumptions and conventional criteria, sample sizes of about 60 subjects per group should be adequate to perform this clinical intervention study successfully and to obtain a conclusive result.

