#### Implementation {16c}

The generation of the allocation will be done by the data management group independently from clinicians.

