### Assignment of interventions: blinding

#### Who will be blinded {17a}

The clinical research group will be blinded against the data analysts. Trial participants cannot be blinded.

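### The plan treats allocation concealment as blinding, so the arm may be known before the phase 2 baseline spirometry that enters the pre-post comparison

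*Protocol article*

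**What the plan says.** Concealment mechanism {16b} sets the order of events. All subjects are first allocated, and only then "each participant will be informed by telephone about the appointment for the phase 2 baseline examination". The section goes on to say that, since immediate and delayed intervention cannot be blinded for study team or participants, "no efforts will be made to conceal this information". Who will be blinded {17a} confirms the position for participants: "Trial participants cannot be blinded".

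Three other statements bear on the point:

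- Implementation {16c}: "The generation of the allocation will be done by the data management group independently from clinicians". Sequence generation {16a} and Interim analyses {21b} place this step after screening and wash-in.
- Trial design {8} describes the outcome measure as blinded, "because the technician does not know to which group (immediate or delayed intervention) the subject belongs to". Procedure for unblinding {17b} likewise calls the trial open-label with blinded outcome assessors.
- Sample size {14} bases the power calculation on the second part of the study, "whereby in both arms assessments before and after treatment are performed", and compares the mean pre-post differences of the two arms.

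**The concern.** Concealment and blinding are different safeguards. Blinding concerns who knows the treatment once it is under way. Concealment concerns who knows the assignment before a participant is irrevocably committed and measured at baseline. Being unable to provide the first is no reason to give up the second.

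Two routes to bias are left open between allocation and baseline:

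1. **Effort.** Forced vital capacity comes from coached forced manoeuvres and depends on how hard the participant tries. A participant who knows whether treatment starts now or in four weeks might try differently. Any average difference between arms goes into the baseline half of the change score.
2. **Attendance.** A participant who knows that treatment is delayed might be less likely to attend. The section on non-adherence and missing data {20c} excludes the data of those who cannot continue, so arm-related loss at this stage would make the analysed groups differ from the allocated ones.

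The planned difference between arms is only one unit (2 against 1), so a modest disturbance at baseline could matter.

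**Working it through.** **Order of events.** Read together, the sections give: screening and wash-in; interim analysis and formation of the groups by the data side; allocation of all subjects; telephone call about the phase 2 baseline; phase 2 baseline; treatment or waiting; follow-up. Two links are inferred. The call is said to convey the appointment; that it may also convey the arm follows from the statement that nothing will be concealed. That pre-treatment spirometry belongs to the phase 2 baseline follows from Sample size {14}, which puts before-and-after assessments in both arms of the second part. The flowchart (Fig. 4), which would settle this, is not shown.

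**Inputs, all from Sample size {14}.** Difference 2 − 1 = 1 unit; variance 1.5 per assessment, so 1.5 + 1.5 = 3 for a pre-post difference and SD √3 = 1.73 (about 1.7 in the text); two-sided alpha 0.05; power 90%; about 60 per group.

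**The plan's own figure.** n per group = 2 × (1.960 + 1.282)² × SD² / 1².

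- SD 1.7: 2 × 10.51 × 2.89 = 60.7, so 61, as stated.
- SD √3: 2 × 10.51 × 3 = 63.0, which rounds up to 64.

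The stated 61 therefore rests on the rounded SD. The present point does not depend on this.

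**Effect of a baseline shift.** If baseline differs between arms by b units for reasons related to knowing the arm, and follow-up is unaffected, the difference in mean change is off by b. The standard error is √(3 × 2/60) = √0.1 = 0.316.

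- Two-sided rejection rate with no true effect: Φ(b/0.316 − 1.96) + Φ(−b/0.316 − 1.96).
- Power when the true difference is 1 and the bias runs against the intervention: Φ((1 − b)/0.316 − 1.96).

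| Assumed shift b (units) | b/SE | False-positive rate | Power if bias opposes the effect |
|---|---|---|---|
| 0 | 0 | 5.0% | 88.5% |
| 0.1 | 0.32 | 6.2% | 81.2% |
| 0.25 | 0.79 | 12.4% | 66.0% |
| 0.5 | 1.58 | 35.3% | 35.2% |

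Using the t distribution instead gives 12.3% and 34.8% for shifts of 0.25 and 0.5. The values of b are assumptions; the documents give none.

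**Dependence on the analysis.** The one-for-one transfer holds for an unadjusted comparison of change. If baseline is a covariate with slope β, the error becomes β × b, which is smaller than b when β lies between 0 and 1. Statistical methods {20a} mentions linear regression, mixed models and GEE without fixing one, so the table applies only if the comparison in the sample size section is the one used.

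**The case against.** A reader might infer from the words on concealment that recruiters could steer patients into a preferred arm. The documents do not support that. Subjects are screened and complete wash-in first, they are allocated as a group, and the list is generated independently of the clinicians. The classic harm of missing concealment is therefore not the main concern here.

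The other counter-arguments are also substantial:

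- The spirometry technician is said to be unaware of the group. The section on spirometry adds three to eight manoeuvres, indices from the best one, visual inspection against acceptability criteria, and repeated tests. These make a systematic difference in effort less likely. They do not exclude it, because the participant knows the arm and may disclose it during coaching.
- Both groups receive the same measures and the delay is four weeks, so neither the direction nor the size of any effort difference can be stated. This stands.
- Non-adherent participants are approached and invited back before exclusion applies. This softens the attendance route but does not close it. Exclusion of losses after allocation is also a wider missing-data question that concealment alone would not resolve.
- Participants must know their arm at follow-up spirometry, so effort-related bias can enter there whatever is done at baseline. This stands, and it limits the benefit of the fix.

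**Conclusion.** The point holds as a limited but real weakness. The article gives a reason for not concealing allocation that does not support the decision, and as written the arm may be known before the baseline measurement. Neither independent generation of the list nor technician blinding covers the participant's own effort or attendance in that interval.

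The size of the bias is unknown. A reader might take from the table that the trial's false-positive rate is 12% or 35%. That would be wrong: those figures follow from assumed shifts of 0.25 and 0.5 units, an unadjusted change-score test, 60 per arm and SD 1.73. They show sensitivity, not expected inflation. Nor do the documents establish that every baseline value is taken with the arm known, since the visit order is inferred. If Fig. 4 shows the pre-treatment spirometry taking place before disclosure, the effort route closes, leaving the attendance route and the faulty reasoning in the text.

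The case for change rests on its low cost rather than on any demonstrated bias.

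**What to change.** Rewrite Concealment mechanism {16b} to separate concealment from blinding:

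- Data management holds the allocation list.
- The phase 2 baseline visit is booked in the same way for every participant, with no indication of the arm.
- The arm is released to participants and clinicians only after baseline spirometry and dental examination are complete, for example by a call to data management or a sealed envelope at the end of that visit.
- The section states explicitly which visit supplies the pre-treatment spirometry.

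With the arm withheld until then, neither effort nor attendance at baseline can depend on knowing it. The sample size is unchanged. The cost is less advance scheduling of the cleaning appointment; whether slots must be held open or booked later depends on the visit layout in Fig. 4. Knowledge of the arm at follow-up spirometry remains unavoidable.

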#### Implementation {16c}

The generation of the allocation will be done by the data management group independently from clinicians.

### Assignment of interventions: blinding

#### Who will be blinded {17a}

The clinical research group will be blinded against the data analysts. Trial participants cannot be blinded.

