### Lung function testing by spirometry

Spirometry prior to bronchodilation will be performed in line with ATS/ERS recommendations [40]. Subjects will sit while wearing nose clips, and the EasyOne Worldspirometer (ndd, Zurich, Switzerland) will be used to obtain flow-volume curves. To obtain optimal flow-volume curves, the participants perform at least three, but no more than eight, manoeuvres under the guidance of specifically trained and experienced examiners. All tests will be visually inspected by experienced physicians according to the ATS/ERS acceptability criteria [40]. Spirometric indices will be taken from the manoeuvre with the largest sum of forced expiratory volume in 1 s (FEV_1_) and forced vital capacity (FVC). Further parameters evaluated will be the ratio of FEV_1_ and FVC (FEV_1_/FVC), and the mean flow rate between 25 and 75% of FVC (FEF_25–75_). Standardized *z*-scores of the lung function parameters FEV_1_, FVC, FEV_1_/FVC and FEF_25–75_ will be calculated based on the reference equations for spirometry from the Global Lung Initiative (GLI—http://www.ers-education.org/guidelines/global-lung-function-initiative.aspx, [48]. After completion of baseline spirometry, subjects will inhale bronchodilator medication according to the ATS/ERS recommendations [40]. Two puffs (each 100 µg) of salbutamol will be delivered into a spacer (volumatic) by a metered-dose inhaler, and the participant will be asked to take five slow and deep breaths over 5–10 s for optimal deposition. Spirometry will be repeated 15 min after salbutamol inhalation. This analysis uses post-bronchodilator lung function data. A positive response is defined as an increase by > 12% and > 200 ml in FEV_1_ and/or FVC post-bronchodilation compared to pre-bronchodilation, according to ATS/ERS standards [40].

Specific attention will be paid to the requirement to obtain very precise and reliable lung function data. In addition to strictly following ATS/ERS recommendations, we will reach the goal of high-quality lung function testing by experienced and well-trained study nurses, the additional visual control by a pulmonologist and the repetition of tests for each subject. There is long-standing, well-documented expertise on lung function assessment in the investigators involved in this study.

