#### Procedure for unblinding if needed {17b}

The design is open-label with only outcome assessors being blinded so unblinding will not occur.

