### Interim analyses {21b}

The study protocol requires interim data analyses after the screening and wash-in phase. This analysis will be carried out by the data analysis group and has to be understood as a prerequisite for forming both intervention groups.

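### The protocol's three statements on blinding conflict, and beyond the spirometry technician it names nobody whose work shapes FVC as unaware of the arm

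*Protocol article*

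**What the plan says.** The Abstract (Methods) and Trial design {8} both state that the intervention is open but the lung function outcome is blind. The reason given in {8} is "because the technician does not know to which group (immediate or delayed intervention) the subject belongs to".

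Three later sections say who is blinded:

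- Concealment mechanism {16b}: the protocol for the two groups "cannot be blinded for the study team and participants, no efforts will be made to conceal this information".
- Who will be blinded {17a}: "The clinical research group will be blinded against the data analysts". It adds that participants cannot be blinded.
- Procedure for unblinding if needed {17b}: "The design is open-label with only outcome assessors being blinded so unblinding will not occur".

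Lung function testing by spirometry describes how a value is obtained. Manoeuvres are done "under the guidance of specifically trained and experienced examiners", with three to eight per test. Then, "All tests will be visually inspected by experienced physicians according to the ATS/ERS acceptability criteria". The section later adds "the additional visual control by a pulmonologist and the repetition of tests for each subject". The indices come from the manoeuvre with the largest sum of FEV1 and FVC.

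On the data side, Implementation {16c} gives generation of the allocation to the data management group, independently of the clinicians. Interim analyses {21b} says of the analysis after screening and wash-in: "This analysis will be carried out by the data analysis group and has to be understood as a prerequisite for forming both intervention groups". Data management {19} and Statistical methods {20a} provide for plausibility checks of the spirometry data. Section {20a} also leaves covariate adjustment and the type of model open.

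**The concern.** Participants and treating staff know the arm, so blinded outcome assessment is the main protection this trial claims for its primary outcome. That protection can be followed and audited only if the protocol says which people are unaware of the arm and at which step. Here the sections give different answers, and the one role named as blind covers only part of the path to an FVC result.

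The effect sought is small: an improvement of 2% under Objectives {7}, and a difference of 1 unit between arms under Sample size {14}. Spirometry is effort-dependent, and accepting or rejecting a manoeuvre can change the recorded value. If such decisions, or later decisions in the analysis, were made with the arm known, they could lean one way while the report still described the outcome as blinded.

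**Working it through.** The protocol gives no figure on this point, so the check is a comparison of texts.

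**Step 1: can {16b}, {17a} and {17b} all be true?** The sentence in {17a} can be read in three ways.

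1. The clinical research group does not know the arm. This conflicts with {16b}, where the study team is not blinded, and with the word *only* in {17b}, unless that group consists solely of outcome assessors. No section says so.
2. The analysts do not know the arm. The sentence has the clinical group, not the analysts, as the party that is blinded. This reading also conflicts with *only* in {17b}, unless analysts count as outcome assessors.
3. The two groups are organisationally separate. This conflicts with nothing, but it is then not a statement about who knows the allocation, and {17a} leaves its own question unanswered for everyone except participants.

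Section {16b} as worded also sits badly with {8}. It abandons concealment for the study team without excepting the technician, on whom the blind in {8} depends.

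**Step 2: which people affect the FVC result, and what is stated about their masking?**

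| Step | Who | Masking stated? |
|---|---|---|
| Guiding the manoeuvres | Examiners, study nurses | Yes for the technician ({8}); whether all examiners are meant is not said |
| Judging acceptability | Physicians | Not named; possibly within the undefined assessors of {17b} |
| Further visual control | Pulmonologist | As above |
| Choosing the manoeuvre | Fixed rule, largest FEV1 + FVC | Not needed for the rule itself, but rejecting the top curve changes what it selects |
| Plausibility checks ({19}, {20a}) | Data staff | No |
| Covariate and model choice ({20a}) | Analysts | No |

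**Step 3: what do {16c} and {21b} add?** The analysis group works on screening and wash-in data before the groups exist. The data management group generates the allocation. Whether these are the same people is not stated. The sections therefore neither show that analysts know the arm nor provide anything that prevents it.

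**Step 4: a purely hypothetical calculation.** It shows sensitivity only and is not an estimate for this trial.

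- Inputs from {14}: variance of each pre-post difference 1.5 + 1.5 = 3; about 60 per group; target difference 2 − 1 = 1.
- Standard error of the difference between arms: √(3/60 + 3/60) = √0.1 = 0.316.
- Invented input: an arm-dependent shift of 0.25 units, a quarter of the target. Then 0.25 / 0.316 = 0.79.
- Two-sided rejection rate with no true effect: P(Z > 1.96 − 0.79) + P(Z < −1.96 − 0.79) = 0.121 + 0.003, about 12% instead of 5%.

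The 0.25 has no source in the documents.

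**The case against.** The strongest reply is that the blind is wider than the technician. Section {17b} speaks of outcome assessors in the plural, and physicians who judge curves against published criteria fit that description. Section {16b} cannot mean everyone in the trial, because {8} and {17b} already exempt some staff. The best-manoeuvre rule and the acceptability criteria limit discretion. Coded reading, disclosure logs and masked analysis are details that an article may leave to the full protocol or analysis plan.

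Much of this stands, and it rules out several stronger readings:

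- A reader might infer that the physicians are known to be aware of the arm. No section places them in the unblinded study team or says they know it.
- A reader might infer that the analysis group forms the arms. Section {21b} gives it only a prior analysis, which reveals nobody's arm, and {16c} gives the allocation to data management.
- A reader might take {17b} as a promise that no participant will ever disclose an arm. It answers the item on code-breaking and says only that no such procedure is needed.
- A reader might suppose that implausible values are excluded. The sections mention checks and do not say what follows from them.

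The reply does not remove the conflict between {16b}, {17a} and {17b}. That lies in what the article states, not in what it leaves out. Nor does it settle whether the curve readers are among the assessors: that reading is possible, but the text does not establish it.

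**Conclusion.** The point holds as a contradiction in the stated blinding, together with an undefined key term. On their ordinary meaning {16b}, {17a} and {17b} do not agree. The technician is the only person named as blind, and nothing stated keeps the curve-reading physicians, the pulmonologist or the analysts from knowing the arm.

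No size can be given. The documents contain no evidence of arm-dependent reading and no figure for it, and the 12% in the working follows only from the invented shift. The importance of the point rests on two things: the small effect sought, and the fact that acceptance of curves and open model choices can influence the FVC result. The open model choice is not itself a finding here, since an analysis plan may settle it; it only makes masking of the analyst more useful. This is a worthwhile and inexpensive correction. It is not a flaw that invalidates the design.

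**What to change.** Rewrite {16b}, {17a} and {17b} so that they give one answer:

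1. Define outcome assessors as the technician and the physicians, including the pulmonologist, who read the curves. Except them from the statement in {16b} that allocation will not be concealed.
2. Give curves to the readers under a code that shows neither arm nor visit. Lock acceptance and the selected manoeuvre before decoding.
3. Have the analyst work with arms labelled A and B until the FVC dataset, including the plausibility checks, is locked. Someone else in the existing data group holds the allocation list.
4. Ask participants not to mention their arm to the technician.
5. Replace the sentence in {17a} with a list of who is unaware of the arm and until when, and claim a blinded outcome only for those steps.

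The cost is some file coding, a change of sequence among existing staff and a short delay before decoding. No additional reader or participant is needed.
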